### Who will take informed consent? {26a}

Potential participants will be identified by a member of the patient’s treatment team, the protocol investigator, or the research team. The principal investigator and study team may also screen the medical records of patients with whom they do not have a treatment relationship for the limited purpose of identifying patients who would be eligible to enroll in the study and to record appropriate contact information to approach these patients regarding the possibility of enrolling in the study (see request for limited waiver of authorization below). A trained member of the research team who is a consenting professional, generally a clinical research coordinator (CRC), will be responsible for screening and consenting participants.

### Additional consent provisions for collection and use of participant data and biological specimens {26b}

As described in the study consent documents (including the verbal consent), deidentified participant data may be used in ancillary studies (i.e., for research that has not been described explicitly to the participant), and they may be shared with other investigators for future research.

## Interventions

### Explanation for the choice of comparators {6b}

#### Information booklet (control)

Participants randomized to the control arm will receive a booklet that includes the information available in the app that can practicably be converted to paper. These participants will not have access to the multimedia aspects of the intervention, such as the videos, but they will have all of the relevant information available in the app described below, including suggestions for accommodations, written templates for letters, links to websites, information about legal protections, and contact information for pro bono legal assistance. The booklet will also contain information about chemotherapy, radiation therapy and surgery, recommendations for management of common symptoms, and advice for communicating with the clinic team. The information booklet will be provided entirely on paper, although participants may independently access websites recommended in the booklet. The booklet content will mirror the app with regard to cultural responsiveness and appropriateness for different job types and characteristics.

### Intervention description {11a}

Our intervention was developed based on data provided by BCW study [7] participants with input from content experts, including our study advisory panel and co-investigators. The 2-pronged approach of the intervention is operationalized through two menus, one focused on interactions with the employer and the other with the clinic team. Each menu has a list of features from which participants can choose to learn about a particular topic. A “My notes” button allows participants to take notes directly on the app. These notes will not be available to the research team, such that participants may use the tool without concerns about privacy.

The work section of the “Learn” tab includes sample videos using trained actors to demonstrate how to approach an employer to request accommodations. Additional features include suggestions for accommodations that may be helpful, templates for letters participants can use when requesting accommodations, links to relevant websites, information about legal protections, and contact information for lawyers and firms that provide pro bono assistance.

The breast cancer section of the “Learn” tab includes information about different common toxicities associated with chemotherapy as well as some information about “what to expect” from radiation therapy and surgery (participants undergoing neoadjuvant chemotherapy will not yet have undergone surgery), recommendations for the management of some of these symptoms (participants reporting symptoms considered urgent will be instructed to contact their oncology providers right away), and advice for communicating with the clinic team (e.g., what kind of information about symptoms the patient should record to share with the provider, including frequency, severity, and associated symptoms and circumstances). This menu also includes examples of ways in which the oncology provider can be helpful with respect to the participant’s work (e.g., providing documentation about the treatment plan or requesting specific accommodations on behalf of the patient) and templates for letters from the oncology provider to the employer. Videos in this part of the app will show examples of interactions with oncology providers, including patients asking for work-related advice and documentation from the provider. The app will also include advice about how to navigate language barriers, including information about accessing an interpreter in the clinic. The app will also show participants the “Tip of the Day,” which will provide helpful information to the TEAMWork app user.

#### Cultural tailoring of the app

The content of the app was developed with the input of both Latina and non-Latina BCW study [7] participants. The text will continue to be adapted and translated using language that is neutral across Latino groups and lacking in idioms, such that people will relate to the content independent of country (and culture) of origin. The Spanish language videos will include actors of different national origins spanning the Latin American countries and territories from which the greatest numbers of Latinas immigrated to New York City. The scripts and expressions used will be familiar to all Spanish-language users but with clear regional derivation. During the usability testing, we will include English and Spanish speakers of different cultural and national backgrounds to ensure that the content is understandable and relatable to our diverse target population.

#### Appropriateness of the app for different job types

The app includes information that is relevant to women in a variety of job situations, many of which are common to different job types, based on a sample from the BCW study [7]. Rather than being sorted by job type (e.g., “retail clerk”), the information is sorted by job characteristics (e.g., “My job requires me to be on my feet for long periods of time”). By sorting the information in this way, participants will more easily be able to access information that is relevant to their specific situation. For example, many retail clerks stand for long periods of time at work. However, this job characteristic is far from universal across all settings in which a retail clerk might work. On the other hand, a nanny or day-care worker who cares for newborn babies may not need to stand for long periods at a time, whereas one who cares for toddlers may need to do so. The app includes a variety of different job characteristics relevant to our target population.

### Criteria for discontinuing or modifying allocated interventions {11b}

Any patient who experiences significant study-related distress or asks to discontinue participation will be removed from the study.

### Strategies to improve adherence to interventions {11c}

Usage tracking analytics will be provided to the study team. These include whether a user accessed the app, which sections were accessed most/least, and the duration of access. During the first 8 months after their study enrollment, participants who have not accessed the app at all during the preceding week will receive targeted “non-use” push notifications encouraging them to use the app and highlighting various app features. Participants may choose to opt out of these notifications. After 8 months, participants may continue to use the app, but they will no longer receive “non-use” notifications, as most will have completed chemotherapy by then.

### Relevant concomitant care permitted or prohibited during the trial {11d}

A potential limitation is the possibility that participants enrolled in the study will access resources extrinsic to the study, which might also affect employment outcomes and symptom control. However, if successful, our intervention will be implemented in a “real-world” setting, in the context of other such resources. Randomization of study participants will help minimize potential bias resulting from the contamination of our study design by external resources. In addition, we will ask participants about other resources they may have accessed and incorporate these data into sensitivity analyses to see how they may have affected our results. This information will be included when we report our study findings to ensure transparency of our study procedures and results.

### Provisions for post-trial care {30}

All research staff will be trained to identify signs of psychological discomfort in the participants. Any patient reporting significant distress (or indicating distress through other signs) will be referred to a licensed or board-certified mental health provider for additional evaluation, support, and/or referrals as needed.

### Outcomes {12}

The primary endpoint of the trial is self-reported employment status 4 months following the completion of treatment. This is the same primary endpoint as was used in the BCW study [7]; timing the assessment of employment status based on the end of treatment rather than the date of diagnosis provides an assessment that is comparable across participants, regardless of the timing between diagnosis and start of treatment. Depending on disease characteristics, provider recommendations, and patient preferences, participants will undergo different chemotherapy regimens with differences in cycle length and total number of cycles. They, therefore, will vary in their overall chemotherapy treatment period. Our endpoint of employment status 4 months following the completion of all treatment, consequently, has a shared interpretation across types of therapy. Two additional assessments will allow us to measure long-term employment status (1 and 2 years after completion of treatment). Patients working full-time or part-time will be considered to be working (job retained) regardless of whether they worked full-time or part-time at baseline.

Secondary study endpoints include change in self-efficacy to ask an employer for accommodations, receipt of workplace accommodations, change in perceived efficacy in patient-physician interactions (PEPPI), and symptom burden. We will ask participants about accommodations requested at baseline and at each on-treatment and post-treatment survey. Those who report asking for accommodations will also be asked to report on whether their request was granted, including whether the request was granted in full, in part, or if they were given a different accommodation instead. Symptom burden will be assessed using relevant items from the Patient-Reported Outcomes version of the Common Terminology Criteria for Adverse Events (PRO-CTCAE®). Details of these analyses are included below. These four secondary outcomes will be evaluated with respect to their relationship with the primary outcome.

The endpoint for the exploratory aim is treatment adherence based on relative dose intensity (RDI), a measure that incorporates both chemotherapy dose-reductions and treatment delays, and for which a standard exists that can be compared across chemotherapy regimens. RDI is expressed as a percent; the commonly accepted threshold below which adjuvant chemotherapy for breast cancer is less effective is 85% [43–45].

### Participant timeline {13}

Timing of procedures and measures for the RCT are provided in Table 1. On-treatment surveys will be administered 5–10 weeks after starting chemotherapy, which will allow for an “on-treatment” assessment that accounts for the wide variation in duration of standard adjuvant chemotherapy regimens for breast cancer. Additional details on measures are included in the section titled “Plans for assessment and collection of outcomes {18a}” below.

**Table 1 Tab1:**
[figure not shown]
SPIRIT figure for randomized controlled trial

### Sample size {14}

*Sample size for Aim 1:* Based on the standards for usability testing codified by Jakob Nielsen and recommended by the Department of Health and Human Services [46–48], an iterative design using 3 waves of 3–4 participants each is needed to optimize usability when 2 distinct groups of users are tested (i.e., English and Spanish speakers). Therefore, we anticipate that we will complete usability testing with 18-24 participants. We will do additional usability testing if significant usability issues continue to be identified during the third wave of usability testing.

*Sample size for Aim 2:* The sample size calculations for the proposed study are based on the findings of the BCW study [7], our prospective, longitudinal, observational study of disparities in employment outcomes. The study sample in BCW [7] is similar to that anticipated for the proposed study (based on eligibility criteria and recruitment sites). In BCW [7], 82% of participants completed 4-month follow-up surveys, 79% completed 1-year follow-up surveys, and 58% completed 2-year follow-up surveys. Based on these data, we anticipate that at least 80–85% of participants in the proposed study who complete baseline assessments will also complete the 4-month assessment and, therefore, be evaluable for the primary endpoint. In contrast to the BCW study [7], which was observational only and in which there was no contact with participants between the baseline and 4-month post-treatment survey, the proposed study is testing an intervention and will include several points of contact throughout the treatment period. We anticipate greater participant engagement in the proposed study and, therefore, higher retention than observed in the BCW study [7]. Nevertheless, for the purposes of sample size calculation, we will use the BCW study [7] retention statistics as a conservative estimate. For the 1- and 2-year endpoints, we expect retention to be at least 80% and 60%, respectively.

In BCW [7], approximately 50% of pre-diagnosis employed women who underwent chemotherapy were working 4 months after treatment completion. The difference in outcome between participants who did and did not have access to paid sick leave through their jobs was approximately 19% and was statistically significant (*p*=0.01). The mechanism of action of our intervention is hypothesized to be that working during the treatment period will provide job security to women and, therefore, lead to long-term job retention. Because paid sick leave provides similar job security, we will use a conservative effect size of 15% for our proposed intervention.

To identify an improvement of 15% in job retention 4 months post-treatment (i.e., 65% job-retention) in the arm randomized to receive the app, we would require 167 evaluable participants in each arm based on a 2-sided test with a 5% type I error and 80% power. We plan to recruit 420 women to obtain primary outcome data from 334 participants (assuming >80% retention 4 months post-treatment). *As noted above, we have estimated 80% retention 1 year post-treatment; we anticipate having higher retention 4 months post-treatment. Thus, we will have at least 80% power and 5% type I error to detect improvements in job-retention of 15% or more 1 year post-treatment. We expect further attrition by year 2. With a conservative 60% retention rate at 2 years, we will have 80% power to detect a difference of at least 17% for job retention at year 2. Using mixed models and important covariates, the detectable effect size for this comparison will likely decrease.*

*Sample size for sub-aim 1:* Characteristics of interest include chemotherapy regimen, symptom burden, race/ethnicity, language, and job tasks. We anticipate that, for example, 35% of participants in the study will have jobs that involve standing for long periods of time. This distribution will allow us to determine whether the association between the app and job retention varies by this job task.

*Sample size for Aim 3:* The percent of participants who express confidence in asking an employer for accommodations will be compared by study arm. This outcome will be evaluated at the mid-point and on the last day of chemotherapy. As a conservative estimate, we expect that 80% of participants will have evaluable data at each of these time-points. Confidence in asking an employer for accommodations based on participant answers to a 5-item scale (see Data collection and management below) will be dichotomized based on the cutoff established in the observational BCW study [7]. Thirty percent of BCW study [7] participants improved their confidence in asking for accommodations between baseline and 4 months post-treatment. In the current study, with a sample size of 167 per arm, we will have 80% power to identify an improvement in confidence of 15% (e.g., 30% of control-arm participants and 45% of those who receive the app) based on a 2-sided test with a 5% type I error.

*Sample size for Aim 4:* Perceived efficacy in patient-physician interactions (PEPPI) at baseline, mid-treatment, and end of chemotherapy treatment will be compared by study arm in 3 *t*-tests. The PEPPI is a 5-item scale (with range 0–50); higher scores indicate greater self-efficacy. In a similar patient sample, the mean was 38 (standard deviation=12). Based on the retention projections described above, we expect to have data for at least *n*=167 per arm at each of the 3 time-points. For each analysis, we will be able to detect a difference from 38 to 42 (>85% power, 2-sided type I error of 5%).

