*Analysis:* To test the TEAMWork App, we have designed a 2-arm, multicenter randomized trial that is stratified by recruitment site and language (English or Spanish). The primary analysis for which this study is powered will be a direct 2-arm comparison of job retention 4 months after treatment completion. Following this, we will fit a multivariable logistic model that includes demographic and clinical variables. Per Kahan and Morris, this model will include the two stratification variables as covariates [63]. Hypothesis testing will be done using the Wald test. We will also evaluate the relationship between job retention and confidence asking for accommodations. To account for chemotherapy-specific differences, we will evaluate the chemotherapy regimen, cycle length, and number of cycles as well as symptom burden in our analyses. To identify the most relevant symptom or symptoms for inclusion in the multivariable model, we will first conduct bivariate analyses and assess the relationship between job retention and the presence of each symptom. These analyses will include symptoms reported by at least 10% of participants. This analysis will include symptoms during the entire treatment period, such that symptoms meeting the above criteria and occurring at any time during treatment will be included. As noted, randomization will be stratified by recruitment site because it is likely there are site-specific similarities that need to be balanced when making an arm-vs-arm comparison of outcomes. However, in further analyses, we will also fit mixed effects logistic regression models where the site can be viewed as a cluster. Parameter estimates from mixed models are adjusted for site-specific correlations. To evaluate long-term endpoints, we will evaluate employment status at 1 and 2 years in similar, separate analyses.

Subaim 1: To evaluate whether the effect of the app on job retention varies by characteristics, such as chemotherapy regimen, symptom burden, race/ethnicity, language, and job type.

*Analysis:* For each of the 3 logistic regressions on job retention (one for each post-treatment time-point), we will evaluate whether there is a significant interaction with the following covariates: chemotherapy regimen, symptom burden, race/ethnicity, language, and job type. Each interaction will be evaluated separately.

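### The protocol says a 35% share of standing jobs lets the trial determine whether the app effect varies by job task, but its own figures give 80% power only for an interaction of about 31–32 points, twice the planned main effect.

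*Protocol article*

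**What the plan says.** Objectives {7} lists Subaim 1, whether the app's effect on job retention differs across patient, treatment and job characteristics. Its whole sample-size justification, in Sample size {14}, is an example of one modifier. The authors anticipate that "35% of participants in the study will have jobs that involve standing for long periods of time" and conclude: "This distribution will allow us to determine whether the association between the app and job retention varies by this job task". No interaction size, power or precision follows. The paragraphs for Aims 2, 3 and 4 each give a detectable difference and a power.

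The sample itself comes from the main effect. The base rate is that "approximately 50% of pre-diagnosis employed women who underwent chemotherapy were working 4 months after treatment completion", the assumed gain is 15 points, and for that "we would require 167 evaluable participants in each arm based on a 2-sided test with a 5% type I error and 80% power".

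Under Statistical methods {20a}, each of the three logistic regressions (4 months, 1 year, 2 years) is examined for a significant interaction with five covariates, and "Each interaction will be evaluated separately". The same section says that the study is powered for the two-arm comparison at 4 months. Only the adherence aim is labelled exploratory; Subaim 1 is not.

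**The concern.** The prevalence of a modifier does not by itself make an interaction test adequate. What matters is the standard error of the difference between subgroup effects against a difference worth finding. A trial sized for 80% power on its main effect has little to spare for a contrast whose standard error is more than twice as large.

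At stake is how a listed sub-aim will be read. If readers have been told that the sample can settle whether the effect varies by job task, a non-significant interaction could be taken to show that the app works equally well in standing and non-standing jobs, although a difference as large as the whole planned effect would probably have been missed.

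**Working it through.** **Inputs from Sample size {14}:** 167 evaluable per arm; job retention 50% (booklet) and 65% (app); two-sided 5%; 80% power; 35% with standing jobs; 420 recruited; 60% retained at 2 years. Allocation is 1:1 (Trial design {8}). The test is an interaction term in a logistic model, for which {20a} specifies Wald tests.

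**1. The plan's own figure.** Unpooled normal approximation: n = (1.960 + 0.842)² × (0.50×0.50 + 0.65×0.35) / 0.15² = 7.849 × 0.4775 / 0.0225 = 166.6, so 167 per arm. It reproduces. (With pooled variance the result is 170.)

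**2. Strata.** 0.35 × 167 = 58.45 and 0.65 × 167 = 108.55 women per arm.

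**3. Standard errors**, taking 50% and 65% in both strata.
- Main effect: √(0.4775/167) = 5.3 points.
- Interaction: √(0.4775/58.45 + 0.4775/108.55) = √(0.00817 + 0.00440) = 11.2 points.
- Ratio: 11.2/5.3 = 2.1, which is 1/√(0.35 × 0.65).

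**4. Detectable interaction at 80% power.**
- Risk-difference scale: 2.80 × 11.2 = 31 points. If the stratum rates differ (no effect in standing jobs, 15 points in the others), the standard error is 11.4 and the result is 32 points.
- Log-odds scale: SE = √[(1/0.25 + 1/0.2275) × (1/58.45 + 1/108.55)] = √(8.396 × 0.02632) = 0.470. The detectable ratio of odds ratios is exp(2.80 × 0.470) = 3.7.

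**5. Power for an assumed interaction.** The protocol gives no size, so 15 points is an assumption borrowed from the main effect. For each configuration below, control retention is 50% in both strata.

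| App effect, standing / other jobs (points) | SE (points) | Power, risk difference | Power, log odds |
|---|---|---|---|
| 0 / 15 | 11.4 | 26.1% | 26.7% |
| 15 / 0 | 11.3 | 26.4% | 26.4% |
| 5.25 / 20.25 (averages 15) | 11.3 | 26.5% | 28.4% |
| 24.75 / 9.75 (averages 15) | 11.0 | 27.7% | 29.7% |
| 30 / 15 | 10.7 | 29.0% | 33.3% |
| 15 / 30 | 10.9 | 27.9% | 34.9% |

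A simulation of the Wald test in the saturated logistic model (200,000 runs per row) gave 26.9%, 26.5%, 28.6%, 29.8%, 33.2% and 34.7%, in the same order. Lower control retention in standing jobs (40% against 55%) gave 26–28%.

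**6. Sensitivity.**
- A 20-point interaction (0 / 20): 42–44%.
- A 30-point interaction: 76–83% over three configurations, consistent with a threshold near 31–32 points.
- All 420 women evaluable, 15 points: 32–35% (risk-difference scale).
- An even 50/50 split, 15 points: 28–31% (risk-difference scale).
- At 2 years, 420 × 0.60 / 2 = 126 per arm: 21–28% for 15 points.
- Evaluable women per arm for 80% power at 15 points: 167 × (31.9/15)² ≈ 755.

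**The case against.** The strongest reply is that the disputed sentence contains no wrong figure. It states no power or effect size and may be only a feasibility remark that the modifier is common enough to examine. {20a} also confines the formal power claim to the primary comparison, and weak interaction tests are usual in a trial sized for its main effect.

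Much of that is right. This is an unsupported statement of adequacy, not an arithmetical slip, and {20a} does limit what is formally powered. But the sentence stands under the sample-size heading as the sole justification for a listed sub-aim, and it says that the trial can determine the answer, not merely look at it. Neither full retention nor an even split makes it true.

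Three stronger readings are tempting, and the document does not support them.
- That a null interaction will be misread. The protocol nowhere says how a non-significant result will be interpreted, so the risk is only that it could be.
- That the trial has a single, fixed power of about 27% for its interaction. That figure depends on the assumed 15 points and on the configuration. The detectable interaction of 31–32 points needs no such benchmark.
- That five covariates at three time-points, or 15 tests, amount to an error of their own. Multiplicity handling for subgroup tests is commonly left to the full protocol or analysis plan, neither of which is shown.

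**Conclusion.** The point holds as a mismatch between a stated capability and the protocol's own inputs. On those inputs, only a difference between subgroup effects of about 31–32 points (ratio of odds ratios about 3.7) would be detected with 80% power at 4 months. If the true difference equalled the planned 15-point main effect, the test would miss it in roughly 65–74% of trials.

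This rests on 167 evaluable women per arm, the 35/65 split being equal in both arms, retention near 50% and 65%, and a test without further covariates. The 15- and 20-point interactions are assumptions, not protocol values. The primary comparison, the recruitment target and the stopping rule are unaffected.

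**What to change.** In Sample size {14}, replace the adequacy sentence with one saying that, at 35% prevalence and 167 evaluable women per arm, an interaction of about 31–32 percentage points would be detectable with 80% power at 4 months, and that smaller differences cannot be reliably detected.

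Label Subaim 1 exploratory in Objectives {7} and {20a}, in line with the statement already in {20a} about what the study is powered for. Report the interaction and subgroup estimates with 95% confidence intervals, and state that a non-significant interaction will not be read as evidence of a uniform effect.

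The cost is one rewritten sentence, a label and a reporting rule. No extra participants, data or design change are needed.
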